#### Outpatient follow-up

The follow-up will be conducted at the outpatient clinic for patients with ICD located in our center. Analysis of records of registered memory device classified as VT/VF episodes will be collected in printed and electronic versions for further investigation by the study team. Medical history will be taken, and a physical examination will be carried out. In case of endpoint VT/VF occurrence during follow-up, the time from NIPS test to ICD episode detection/therapy will be measured. The follow-up will last one year and will be conducted every 3 months; thus, each patient will have four visits – one at 3, 6, 9 and 12 months after performing NIPS. The following parameters will be collected:The patient’s clinical status will be determined on the basis of a physical examination, NYHA class, changes in medication, hospitalizations, cardiac events such as syncope, ICD discharges, palpitations and other, which occurred after the previous visit.The ICD memory will be examined, and all events will be analyzed. All ICD interventions will be analyzed and classified as appropriate or inappropriate. The type of cardiac rhythm (VF, VT, or other) and the cycle length and duration will be also measured.All follow-up visits and data collection will be performed by the principal investigator (PF). If necessary, drug therapy will be modified during follow-up, but the result of the NIPS will not be taken into account when changes in the antiarrhythmic drug therapy are considered. Changes in ICD programming will be possible; however, these will be based on arrhythmic events occurring during follow-up and not based on the results of the NIPS.

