### Expected results

During the NIPS the following clinical situations are expected to occur:lack of induction of arrhythmia (negative result)induction of ventricular extrasystoles (negative result)induction of hemodynamically stable nsVT (negative result)induction of hemodynamically unstable nsVT (positive result)sVT induction (positive result)VF induction (positive result).

It is expected that appropriate ICD interventions during follow-up will occur more often in patients who had sustained ventricular arrhythmias induced during NIPS (positive result). The primary endpoint of the follow-up will be appropriate intervention of ICD or sudden cardiac (arrhythmic) death; the secondary, appropriate ICD intervention or death from cardiovascular causes; and the tertiary, appropriate ICD intervention, death or hospitalization for cardiovascular causes. Because all patients will remain under the study follow-up for 1 year, the degree of exposure to arrhythmia recurrence (arrhythmia burden) will be determined defined as the number of relevant interventions during the year of observation.

Appropriate ICD intervention is defined as the high or low energy treatment due to the occurrence and detection of VT/VF.

For death from cardiovascular causes, it is considered death due to VF, extensive myocardial infarction, end-stage heart failure, or electromechanical dissociation or asystole due to presumed cardiovascular cause.

For sudden cardiac (arrhythmic) death, death due to sVT/VF or, in the absence of available documentation, death that occurred within 1 hour of the onset of symptoms [29] may be considered. Every effort will be made to interrogate ICD postmortem in order to establish the mode of death.

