### Limitations

The study has some limitations. First, although all consecutive patients attending our outpatient clinic will be invited to the study, probably not all will give consent to enter the trial. Thus, the study group will consist of all consecutive patients who agreed to participate in the study but not of all our patients with ICD. However, a logbook including all ICD patients will be maintained, so we will know exactly what percentage of our ICD patients entered the study. Secondly, the physician performing follow-up visits will not be blinded to the results of NIPS. However, as a rule, medication or ICD programming will not be influenced by NIPS results because there are no data indicating that this should be done. It is our and similar studies which should shed more light on this issue and answer the question whether NIPS results can be taken into account when medication and ICD programming changes are concerned.

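### The follow-up investigator knows the NIPS result, and the stated safeguards cover drugs and ICD programming but not classification of the endpoint

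*Protocol article*

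**What the plan says.** The Outpatient follow-up section of the protocol article puts one person in charge: "All follow-up visits and data collection will be performed by the principal investigator". Limitations adds that "the physician performing follow-up visits will not be blinded to the results of NIPS".

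On the outcome, Outpatient follow-up states: "All ICD interventions will be analyzed and classified as appropriate or inappropriate". The sentence names no classifier. The same section says that device records of VT/VF episodes "will be collected in printed and electronic versions for further investigation by the study team", and does not say whether that team knows the NIPS result.

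Expected results makes the classification part of the outcome: "The primary endpoint of the follow-up will be appropriate intervention of ICD or sudden cardiac (arrhythmic) death". The secondary and tertiary endpoints also contain appropriate intervention. An appropriate intervention is defined there as high- or low-energy therapy given because VT/VF occurred and was detected. An undocumented death within one hour of symptom onset can be counted as sudden cardiac death, in permissive rather than mandatory wording.

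The safeguards tied to knowledge of NIPS are three:
- for drugs, "the result of the NIPS will not be taken into account when changes in the antiarrhythmic drug therapy are considered";
- for changes in programming, "these will be based on arrhythmic events occurring during follow-up and not based on the results of the NIPS";
- in Limitations, directly after the unblinding is conceded, "as a rule, medication or ICD programming will not be influenced by NIPS results".

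**The concern.** Statistical methods makes the relationship between a positive NIPS result and the follow-up outcome the principal analysis. The person who gathers all outcome data therefore knows the predictor under test. The article also states the expected direction in advance: more appropriate interventions in NIPS-positive patients.

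Knowledge of NIPS can act by two separate routes. It can change treatment or programming, and so change what happens to the patient. It can also change how an episode or death is read, and so change what is recorded. The safeguards answer the first route only. If the second operates, a doubtful episode may be called appropriate more readily in a NIPS-positive patient and less readily in a NIPS-negative one. Either shift would raise the apparent association, sensitivity and predictive value.

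**Working it through.** **1. Where judgement enters, and what protects it**

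| Step | What the article fixes | Protection against knowledge of NIPS |
|---|---|---|
| Drug changes | Possible during follow-up | Stated |
| Programming changes | Possible during follow-up | Stated |
| Visits and data collection | One unblinded investigator | None stated |
| Appropriate or inappropriate | Classified; classifier not named | None stated |
| Undocumented sudden death | One-hour rule, permissive wording | None stated |

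Appropriateness turns on the rhythm, and Outpatient follow-up allows VF, VT or other. Under The study group, AF excludes a patient only when it is persistent or long-standing without effective anticoagulation. Therapy for a non-ventricular rhythm is therefore plausible.

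**2. The 2×2 table implied by the plan's inputs (Statistical methods)**

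- Expected events: 150 × 0.067 = 10.05, about 10, leaving 140 patients without an event.
- NIPS positive among those with an event: 0.30 × 10 = 3.
- NIPS positive among those without: 0.079 × 140 = 11.06, about 11.
- Hence 3 + 11 = 14 positives with 3 events, and 150 − 14 = 136 negatives with 10 − 3 = 7 events.

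Uncorrected chi-square = N(ad − bc)² / (product of the four margins), with a, b = events and non-events in positives and c, d = the same in negatives:

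150 × (3×129 − 11×7)² / (14 × 136 × 10 × 140) = 150 × 310² / 2,665,600 = 5.41, p = 0.020.

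This agrees with the plan's statement that 150 patients suffice for P < 0.05, in the sense that the expected table is significant by that test. The plan states no power, so the sample size itself cannot be reproduced.

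**3. Moving one patient's classification**

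Risk ratio = (events/14) ÷ (events/136). Sensitivity = events in positives ÷ all events.

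| Events, positives | Events, negatives | Risk ratio | Sensitivity | Chi-square p (uncorrected) | Fisher p |
|---|---|---|---|---|---|
| 2/14 | 7/136 | 2.8 | 2/9 = 22% | 0.17 | 0.199 |
| 3/14 | 7/136 | 4.2 | 3/10 = 30% | 0.020 | 0.053 |
| 4/14 | 7/136 | 5.6 | 4/11 = 36% | 0.0014 | 0.011 |
| 3/14 | 6/136 | 4.9 | 3/9 = 33% | 0.011 | 0.039 |

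Against the expected table (second row), one fewer event among positives takes the chi-square result from significant to non-significant. One more among positives, or one fewer among negatives, takes the Fisher result from non-significant to significant.

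**The case against.** Several points on the other side stand.

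- **It is disclosed.** Limitations states the unblinding openly. But the defence offered there answers only treatment and programming, so disclosure does not cover classification.
- **The classifier is not named.** A reader might infer that the unblinded investigator alone classifies the endpoints, or that masked reading has been rejected. The text supports neither. The classifying sentence is passive, records also go to the study team, and a journal article may leave adjudication detail to a fuller protocol. What the article does fix is an unblinded data collector and safeguards that leave the endpoint out.
- **The endpoint is largely device-recorded.** Stored episodes, measured cycle length and duration, a written definition and the commitment to attempt post-mortem interrogation all limit discretion. Judgement remains over rhythm and undocumented deaths. The article gives no figure for how many cases would be ambiguous.
- **The p-values measure fragility.** Ten events would be fragile under perfect masking too. The endpoint is per patient, so one reading matters only where a patient's status rests on a single doubtful episode or death. The expected count of events among positives is 14 × 10/150 = 0.93, so the uncorrected chi-square is a poor approximation, and the planned endpoint comparison is a log-rank test. Where the 0.05 line is crossed depends on the test: between 2 and 3 events by chi-square, between 3 and 4 by Fisher. One event is enough under either.

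**Conclusion.** The concern holds in a limited form. One investigator who is not blinded to NIPS does all follow-up and data collection. The endpoints need judgement, and the stated safeguards do not reach it. Knowledge of NIPS may therefore inflate its apparent predictive value.

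A reader might go further and conclude that NIPS knowledge does inflate the result, or that one judgement will decide the trial. The documents do not support that: they give no rate of ambiguous episodes and no evidence of differential reading. The calculation shows only that, with about 10 events, one patient reclassified can move p across 0.05 and sensitivity between roughly 22% and 36%. It assumes the plan's own rates (6.7%, 30% and 7.9%), rounded to whole patients, with two-sided testing and simple 2×2 tests in place of the log-rank test.

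This is a design weakness that should be corrected because correction is cheap. It is not an error that invalidates the plan.

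**What to change.** 1. **Classification of record.** State that interventions and deaths are classified from the device records already being collected and from death documents, coded and with the NIPS result removed. Include every device-treated episode and not only those already labelled VT/VF, since the article does not say whether the device or a person applies that label. The reader should be an existing study-team member who did not attend that patient's NIPS, where one is available. The article does not show that one exists, so any patient for whom this was not possible should be reported.
2. **Sensitivity analysis.** Prespecify time to first device-delivered therapy (ATP or shock) in a programmed VT/VF zone, whatever its class, or death from any cause. This needs no judgement of appropriateness or mode of death.
3. **Limitations.** Extend the paragraph on unblinding to endpoint classification.

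The cost is a little record preparation and one extra analysis, with no new visit or procedure. The sensitivity endpoint will include some inappropriate therapies and non-arrhythmic deaths, and it still depends on device programming, which may change during follow-up. It therefore supports the primary analysis and does not replace it.

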### Expected results

During the NIPS the following clinical situations are expected to occur:lack of induction of arrhythmia (negative result)induction of ventricular extrasystoles (negative result)induction of hemodynamically stable nsVT (negative result)induction of hemodynamically unstable nsVT (positive result)sVT induction (positive result)VF induction (positive result).

It is expected that appropriate ICD interventions during follow-up will occur more often in patients who had sustained ventricular arrhythmias induced during NIPS (positive result). The primary endpoint of the follow-up will be appropriate intervention of ICD or sudden cardiac (arrhythmic) death; the secondary, appropriate ICD intervention or death from cardiovascular causes; and the tertiary, appropriate ICD intervention, death or hospitalization for cardiovascular causes. Because all patients will remain under the study follow-up for 1 year, the degree of exposure to arrhythmia recurrence (arrhythmia burden) will be determined defined as the number of relevant interventions during the year of observation.

Appropriate ICD intervention is defined as the high or low energy treatment due to the occurrence and detection of VT/VF.

For death from cardiovascular causes, it is considered death due to VF, extensive myocardial infarction, end-stage heart failure, or electromechanical dissociation or asystole due to presumed cardiovascular cause.

For sudden cardiac (arrhythmic) death, death due to sVT/VF or, in the absence of available documentation, death that occurred within 1 hour of the onset of symptoms [29] may be considered. Every effort will be made to interrogate ICD postmortem in order to establish the mode of death.

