If the test induces sustained ventricular arrhythmia, after the sinus rhythm has been restored, the patient will be transferred to the intensive care room, where at the time of his stay, continuous ECG and blood pressure will be performed.

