## Discussion

This study will provide information regarding the result of NIPS on the occurrence of life-threatening arrhythmic events in patients with ICD. It is expected that appropriate ICD interventions during follow-up will occur more often in patients who had sustained ventricular arrhythmias induced during NIPS. Consequently, these patients may require more aggressive antiarrhythmic therapy or prophylactic ablation of arrhythmia substrate to prevent the occurrence of arrhythmias and ICD discharges.

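### The tertiary endpoint counts any cardiovascular hospitalization, so an admission prompted by a positive NIPS result would count as an event, and the no-influence rule does not cover admission decisions

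*Protocol article*

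**What the plan says.** The Expected results section of the protocol article sets three nested endpoints. The first is given as "The primary endpoint of the follow-up will be appropriate intervention of ICD or sudden cardiac (arrhythmic) death". The second pairs appropriate ICD intervention with cardiovascular death. The third is "the tertiary, appropriate ICD intervention, death or hospitalization for cardiovascular causes". Only the third contains hospitalization, and the text does not separate planned from unplanned admissions, or admissions caused by the test result from others.

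The safeguard is in Outpatient follow-up. For medication, "the result of the NIPS will not be taken into account when changes in the antiarrhythmic drug therapy are considered". For device settings, changes are allowed but "these will be based on arrhythmic events occurring during follow-up and not based on the results of the NIPS". The Limitations section repeats the same two items, medication and programming, and presents them as a general rule. Neither section mentions ablation or the decision to admit.

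Outpatient follow-up also says that a single investigator carries out all visits and data collection, and that hospitalizations since the last visit are recorded each time. Limitations states that this physician is not blinded to NIPS.

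**The concern.** The study asks whether a positive NIPS result predicts later events. That question is answered fairly only if the result cannot itself produce an event. For drugs and programming the article closes this route. For admissions it does not: the endpoint is broader than the safeguard, and the person who could respond to a positive result also collects the outcome. An elective stay for observation, work-up or a procedure, arranged because the test was positive, meets the tertiary definition as worded. NIPS-negative patients have no matching route.

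The tertiary comparison could then show an association even if NIPS had no prognostic value. If a prompted admission led to ablation, a second and opposite effect would follow. Ablation is meant to reduce later arrhythmia and ICD therapy, so it would tend to dilute the primary comparison.

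**Working it through.** **Step 1: scope of endpoint against scope of safeguard.**

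| Possible response to a positive result | Covered by the no-influence rule? | Can it be a tertiary event as worded? |
|---|---|---|
| Antiarrhythmic drug change | Yes | Not in itself |
| ICD reprogramming | Yes | Not in itself |
| Discretionary cardiovascular admission | Not named | Yes |
| Ablation during follow-up | Not named | Yes, through the admission |

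The last two rows are the gap.

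**Step 2: group sizes implied by the plan.** Statistical methods gives 150 patients, a primary event rate of 6.7%, and a positive NIPS in 30% of patients with an event and 7.9% of those without.

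- Patients with an event: 150 × 0.067 = 10.05, about 10. Patients without: about 140.
- Positive NIPS: 10 × 0.30 = 3, plus 140 × 0.079 = 11.06, about 11. Total about 14.
- Negative NIPS: 150 − 14 = 136.

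On this expected table (3 of 10 against 11 of 140) the uncorrected chi-square is 5.41, p = 0.020. That agrees with the article's statement that 150 patients suffice for P < 0.05. No power is stated, so the sample size itself cannot be reproduced, and this point does not depend on it.

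**Step 3: effect of a few prompted admissions.** The article gives no tertiary rate. Assume 20% in both groups, so no true association, and let k of the 14 positive patients have a prompted admission independently of their other events. The observed rate in positives is 0.20 + 0.80 × k/14, and the ratio is that rate divided by 0.20.

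| k | Rate in positives | Spurious ratio |
|---|---|---|
| 0 | 0.200 | 1.00 |
| 1 | 0.257 | 1.29 |
| 2 | 0.314 | 1.57 |
| 3 | 0.371 | 1.86 |

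**Step 4: range over the unknown base rate.** Let r be the true tertiary rate in both groups and f the share of positives admitted because of the result. The rate in positives is r + f(1 − r). The chance of p < 0.05 was found by exact binomial enumeration with 14 positives and 136 negatives, using the uncorrected chi-square test. The planned log-rank test would give somewhat different values.

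| r | Ratio, f = 10% | Chance of p < 0.05 | Ratio, f = 20% | Chance of p < 0.05 |
|---|---|---|---|---|
| 6.7% | 2.4 | 28% | 3.8 | 59% |
| 10% | 1.9 | 22% | 2.8 | 50% |
| 20% | 1.4 | 14% | 1.8 | 31% |
| 30% | 1.2 | 10% | 1.5 | 21% |

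With f = 0 the chance is about 4% to 5% in every row. The 6.7% row is the plan's primary event rate. The tertiary endpoint is broader, so its rate should be at least that. With 14 positives, f = 10% is 1.4 patients and f = 20% is 2.8.

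**The case against.** The strongest reply is that the article plans no care driven by NIPS. The Discussion says "these patients may require more aggressive antiarrhythmic therapy or prophylactic ablation of arrhythmia substrate", and a reader might infer that positive patients will be sent for ablation during the study. The text does not support that. The sentence describes what could follow from the study's findings, not management within it. Background refers to vulnerable patients in general and adds that prophylactic ablation has not entered daily practice. The Discussion and the no-influence rule do not contradict each other. This part of the reply stands: the gap is silence, not a stated practice.

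Two stronger readings are also tempting. First, the definition "Appropriate ICD intervention is defined as the high or low energy treatment due to the occurrence and detection of VT/VF" does not say spontaneous, so a reader might infer that therapy delivered during the test counts as an endpoint. It should not be read that way. NIPS methodology records ATP and cardioversion of induced arrhythmia as test parameters, and the endpoints belong to follow-up: "In case of endpoint VT/VF occurrence during follow-up, the time from NIPS test to ICD episode detection/therapy will be measured". The plan's own inputs also expect about 11 of 14 positives to have no primary event, which would make little sense if therapies for induced VT/VF counted.

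Second, "If the test induces sustained ventricular arrhythmia, after the sinus rhythm has been restored, the patient will be transferred to the intensive care room" might suggest that this stay is a tertiary hospitalization. But every patient, positive or negative, is already admitted for the test, and the transfer takes place within that admission.

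It can also be said that adjudication rules for hospitalization are commonly left to a full protocol or analysis plan, which is not shown. They may well be there. However, the article does state both the endpoint and the safeguard, and as stated their scopes do not match. Finally, the number of prompted admissions is unknown and may be zero.

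**Conclusion.** The point holds for one route and one endpoint. As worded, a discretionary cardiovascular admission prompted by a positive NIPS is a tertiary event, and neither the no-influence rule nor blinding stands in the way. The bias is toward an association. The hospitalization route does not touch the primary or secondary endpoint, which limits its weight.

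The size is conditional. The 14 positives follow from the plan's figures. The 20% base rate and the one to three prompted admissions do not, and nothing shows that such admissions are expected. What the calculation does show is sensitivity: with so few positives, two or three admissions are enough to produce a misleading tertiary result. The possible dilution of the primary comparison depends on ablation actually being done in positive patients during follow-up, which the article neither plans nor rules out.

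**What to change.** - In Expected results, limit the hospitalization component of the tertiary endpoint to unplanned cardiovascular admissions after discharge from the NIPS stay. Report elective and NIPS-prompted admissions separately.
- Record the reason for each admission. Whether an admission was unplanned will still be judged by an unblinded investigator, and a recorded reason makes that judgement checkable.
- Record any ablation during follow-up with its date and reason. Add a sensitivity analysis of the primary endpoint with follow-up censored at ablation, noting that such censoring may be informative.
- The sponsor should state in Outpatient follow-up and Limitations whether the no-influence rule extends to ablation and admission decisions. Which way that is settled is for the sponsor.

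The cost is a few sentences and one extra analysis. Hospitalizations are already collected at every visit. The downside is slightly fewer tertiary events. Little should be lost, because an elective ablation admission for spontaneous VT would usually follow an ICD intervention that already counts in the composite.

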### Statistical methods

The principal analysis will examine the relationship between positive NIPS result and the follow-up outcome. Further subanalyses will also take into account the protocol stage at which arrhythmia was induced as well as the tachycardia cycle length and duration. At the first stage, groups of patients will be extracted by the occurrence of arrhythmic events during NIPS,- as in section 4. Afterwards, these groups will be compared according to the data collected during the follow-up (endpoints). The group, in which the endpoints occurred, will be compared with a group of patients without endpoints according to the NIPS result using Kaplan–Meier survival curves and tested with a log-rank test. A P value of 0.05 will be considered statistically significant for all analyses.

Next, with Multivariate Cox Proportional Hazards Model the presence or absence of the NIPS result correlation will be determined with other risk factors affecting the possibility of developing adequate ICD interventions that have been previously described in the available literature and widely accepted, that is, echocardiogram result, NYHA class, the presence of atrial fibrillation, renal function, width of native QRS complexes. The sensitivity, specificity, positive, and negative predictive value in predicting the occurrence of NIPS endpoints also will be calculated using Student’s t test or the Mann–Whitney test for continuous variables, where appropriate.

With the chi-square test, 150 patients have been estimated as needed for inclusion in the study. This assumption is based on the calculation that primary endpoints will occur in 6.7 % patients, and the result of NIPS will be abnormal in 30 % of those patients and in 7.9 % of patients without VT/VF recurrences [2, 30, 31]. This number of patients will be sufficient to demonstrate significant difference (*P* < 0.05) between the groups.

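### Arrhythmia burden is a raw one-year count that assumes every patient is followed for a year, although all three endpoints include death

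*Protocol article*

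**What the plan says.** Under Expected results, the article introduces arrhythmia burden with the premise "Because all patients will remain under the study follow-up for 1 year" and says that burden is "defined as the number of relevant interventions during the year of observation". No time at risk enters the definition.

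The same section names three endpoints, each with a death component:

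- For the primary: "The primary endpoint of the follow-up will be appropriate intervention of ICD or sudden cardiac (arrhythmic) death".
- The second-ranked endpoint keeps the device component and widens the fatal part to any cardiovascular death.
- The third-ranked one again includes death and adds hospital admission: "the tertiary, appropriate ICD intervention, death or hospitalization for cardiovascular causes".

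It also foresees deaths in practical terms: "Every effort will be made to interrogate ICD postmortem in order to establish the mode of death".

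Outpatient follow-up sets the schedule, "The follow-up will last one year and will be conducted every 3 months", and gives each patient four visits.

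Statistical methods applies Kaplan–Meier curves, the log-rank test and a Cox model to the endpoints. It does not mention burden.

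**The concern.** A count per person can be compared across patients without a denominator only if everyone is observed for the same time. The article relies on exactly that and says so. Yet a study that counts deaths as outcomes expects some patients to stop contributing before month 12. Their counts stop too, while the definition still treats the count as a year's worth.

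The truncation is unlikely to be neutral. The article's hypothesis is that NIPS-positive patients have more life-threatening arrhythmia, and death from VF or sustained VT is one of the outcomes. If those patients also die sooner, their counts are cut more often, and a real difference in burden looks smaller than it is. Patients who withdraw or are lost add shortened counts in the same way.

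**Working it through.** The article gives no expected burden, no mortality and no withdrawal rate, so there is no stated figure to reproduce. The 6.7% in Statistical methods ("primary endpoints will occur in 6.7 % patients") combines interventions with arrhythmic deaths and is not split, so it cannot serve as a mortality figure. Every mortality value below is an assumption.

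**1. The texts side by side.** The premise has all patients in follow-up for a year. The endpoints and the post-mortem interrogation have some patients dying within that year. Both cannot hold as written, and the raw count rests on the premise.

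**2. One patient.** With a steady intervention rate, death at month 3, 6 or 9 leaves 3/12 = 25%, 6/12 = 50% or 9/12 = 75% of the full-year count.

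**3. A group, with death unrelated to intervention rate.** With a constant death hazard and one-year mortality m, mean time at risk is m / (−ln(1 − m)) years. The expected raw count is the annual rate times this.

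| Assumed m | Mean exposure (years) | Raw count below annual rate |
|---|---|---|
| 5% | 0.05 / 0.0513 = 0.975 | 2.5% |
| 10% | 0.10 / 0.1054 = 0.949 | 5.1% |
| 20% | 0.20 / 0.2231 = 0.896 | 10.4% |

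**4. The contrast.** Take an assumed true rate ratio of 2.0, NIPS-positive to NIPS-negative.

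- Mortality 10% against 3%: 2.0 × 0.949 / 0.985 = 1.93.
- Mortality 20% against 5%: 2.0 × 0.896 / 0.975 = 1.84.
- Equal mortality: the ratio stays at 2.0. The attenuation needs a difference in mortality.

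**5. A group, with death and interventions sharing a cause.** Let both rates scale with a gamma frailty of mean 1 and variance 1, and let the average death hazard be a per year. The proportion dying is a/(1 + a). The expected count is 1/(1 + a) of the full-year value. For a = 0.05, 0.10 and 0.20, 4.8%, 9.1% and 16.7% die, and the count falls short by the same percentages.

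A pooled rate per patient-year repairs only part of this. For a = 0.10, mean exposure is ln(1.10)/0.10 = 0.953 years. The rate is then 0.909 / 0.953 = 0.954 of the true one, still 4.6% short.

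**6. Scale of the NIPS-positive group.** Statistical methods implies about 0.067 × 150 = 10 patients with a primary endpoint and 140 without. It then implies 0.30 × 10 + 0.079 × 140 = 3 + 11.06, or about 14 NIPS-positive patients. One death at mid-year removes 0.5/14 = 3.6% of that group's exposure.

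**The case against.** Four points can be made for the plan.

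- **Burden is peripheral.** It appears once, is not one of the three endpoints, and Statistical methods plans no test of it. This stands. A reader might infer that the main comparison by NIPS result is biased. The article does not support that, because Kaplan–Meier, log-rank and Cox methods can accommodate unequal follow-up.
- **The premise may only mean a common one-year window**, with the handling of deaths left to a fuller document. That would explain an omission. It does not rescue a reason that is stated and wrong, and an analysis plan that followed the text would inherit it.
- **The raw count can be a legitimate target.** Interventions actually experienced by month 12, with none after death, is a valid quantity. If death is the only reason follow-up stops, the mean raw count equals the mean cumulative function at 12 months with death as terminal event. This also stands: the count is understated relative to full-year exposure, not under every definition. The article, however, does not choose this target. It justifies the count by complete follow-up.
- **A rate is no cure.** Dividing by time at risk does not remove informative truncation (step 5), and it inflates the result for a patient who dies early after a cluster of interventions. This limits what the fix can claim.

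Two further readings are tempting. One is that the t test or Mann–Whitney test is meant for the burden count, so that one patient with many episodes could drive the result. The sentence naming those tests concerns sensitivity, specificity and predictive values, and neither test is assigned to burden. The other is that a negative binomial model is required. With about 10 patients expected to have a primary endpoint, that is a preference the documents do not compel.

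**Conclusion.** The point holds as an internal contradiction with a modest effect. The equal-follow-up premise conflicts with the death components in the same section, and the burden count has no denominator to absorb the difference. Relative to a full year at risk, the shortfall is about 2.5% to 5% at 5% to 10% one-year mortality and about 10% at 20%, given a constant hazard unrelated to intervention rate. It is larger if the patients with most interventions also die most often. Attenuation between NIPS groups is conditional: it arises if NIPS-positive patients die sooner, which is plausible under the article's hypothesis but not shown by any figure in it. The defect is confined to a supplementary measure and leaves the primary analysis as it is.

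**What to change.** 1. Delete the statement that all patients stay in follow-up for a year.
2. Define burden as the number of appropriate ICD interventions from NIPS to the earliest of 12 months, death or last device interrogation.
3. Report it with observed follow-up time, and say which quantity is meant. A rate per patient-year describes intensity while alive and observed. A mean cumulative function, with death as terminal event and losses censored, describes interventions experienced by month 12.
4. Show deaths by NIPS group beside the burden result, because a rate alone does not deal with truncation by death.

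The cost is a change of wording and a little extra analysis. The article already plans to collect device episodes with their time from NIPS, visits every three months and post-mortem interrogation where possible, so no new data or visits are needed. The downside is that rates are unstable for patients who die very early, so pooled group rates are safer than averages of individual rates.
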